
### Data Management and Quality Assurance

Data generated will be accessible only to the research team. All data will be collected and managed using the secure, web-based software platform REDCap [26,38], hosted at The University of Manchester. The data collection forms in REDCap will use functions that check for mandatory information, data ranges, and alerts whenever data violate specific limits [38]. Paper documents, such as written consent forms, will be stored in a locked cabinet in a secure area.

Digital copies of data will be stored securely using the University of Manchester’s Research Data Storage (RDS) service while pending, during, and following analysis. Any physical copies of the data will be stored in a locked filing cabinet within a locked office building on the university campus.

Study data and materials may be looked at by individuals from the University of Manchester, regulatory authorities, or the NHS Trust for monitoring and auditing purposes, and this may well include access to personal information. A member of the participant’s care team trained for this study may also gain access to these data where essential for the identification of an individual participant.

A unique alphanumeric identification code, and subsequently a pseudonym, will be assigned for each participant. Data entry will be checked for completeness intermittently throughout the study by a researcher not involved in data collection (CS), and a trial monitoring team, independent from the sponsor and funder, will monitor progress and data management procedures every month. Direct quotations from interviews or focus groups may be used, but these will be anonymized prior to publication and in interview transcripts. Participants will be given pseudonyms in transcripts and publications.

### Sample Size

Parameter estimates are based on a previous study of a digital intervention for adults in community settings with BBS as the primary outcome measure at 12 weeks [12]. Based on data from this previous study, we estimate the SD to be 14. Correlation between baseline and follow-up was 0.81 in the previous trial, but we will use a conservative value of 0.7. To achieve 90% power at a 5% significance level, with inflation for 13% attrition, we estimate that a sample size of 196 (98 per arm) is required to demonstrate the minimal clinically important change needed to reduce falls risk and improve functional balance of a difference in means of 5 points on the BBS at 12 weeks [39]. A minimal clinically important change of 5 points in the BBS was chosen according to baseline BBS scores of 35 to 44 observed in a previous study of older adults in the same region where the trial will be conducted [12].

### Adverse Events and Risk

The main concern regarding adverse events and/or risk is whether or not the participant can come to any harm from using the KOKU digital program. No disproportionate adverse events are expected, as all of the exercises within the KOKU digital program have been well researched with older people and mimic those of a routine physiotherapy session. Participants will be trained on how to use KOKU safely and will be requested to inform the Principal Investigator in the event of any injury, after seeking appropriate medical assistance. Any participant suspected of having an adverse reaction will be immediately withdrawn from the study, with the cause of the event thoroughly investigated. The Principal Investigator will determine seriousness and causality in conjunction with any treating medical practitioners. A serious adverse event that is deemed directly related to, or suspected to be related to, the trial intervention will be reported to the ethics committee. All trial staff in contact with participants will be responsible for recording adverse events, and the adverse event procedure will be followed.

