The Five Times Sit-to-Stand (5-STS) chair test [28] will be completed to assess lower limb strength. For this test, the participant is asked to stand up and sit down as quickly as possible 5 times from a standard-height chair (43.2 cm) with their arms folded. The researcher records the time taken to complete the test.Health-related quality of life will be measured using the EQ-5D-5L [29], which considers 5 dimensions: mobility, self-care, usual activities, pain or discomfort, and anxiety. Each dimension is rated as one of the following 5 options: no problems, slight problems, moderate problems, severe problems, and extreme problems.Mood will be assessed using the 5-item Geriatric Depression Scale. This screening tool for depression in older adults is validated to be as effective as the 15-item Geriatric Depression Scale in a wide range of settings [30].The level of physical activity will be measured using the Physical Activity Scale for the Elderly questionnaire [31]. This is a validated and easy-to-administer questionnaire designed to assess physical activity in those 65 years and older.Concerns about falling will be measured using the Short Falls Efficacy Scale—International [32]. The Short Falls Efficacy Scale—International is a validated and reliable 7-item tool that measures concerns about falling in relation to a range of everyday activities and is available in a number of languages [32,33].The risk of falling will be assessed using the assessment of falls risk tool. This validated measure [34] has 5 items, which include a history of any fall in the previous year, 4 or more prescribed medications, diagnosis of stroke or Parkinson disease, reported problems with balance, and inability to rise from a chair without using arms. A visual analog score for pain and fatigue will be included, as these are all strong indicators of risk of falling.Secondary outcomes will also consider the usability and acceptability of KOKU. At the 12-week assessment, participants in the intervention group will complete questionnaires focusing on usability, acceptability, and motivation to use KOKU. The System Usability Scale will assess the usability of KOKU from the users’ perspective [35]. The theoretical framework for acceptability will assess perceived acceptability of the KOKU system [36]. The short version of the User Experience Questionnaire will assess the usability of the KOKU system [37].Falls will be assessed using daily self-report fall calendars for 24 weeks, with follow-up phone calls from a researcher to find out more details of any falls reported and any use of health care resources. This will include details on how the fall occurred, if a visit to a general practitioner (GP), hospital, or emergency department was required, and if the fall resulted in a fracture, swelling, or other self-reported injury. Fall severity will be coded as no injury, moderate injury, or serious injury based on consultation between 2 authors (CF, ES), including a registered nurse and without discussion of group allocation. Falls and all injuries will be recorded during the 6-month period, with falls defined as “an unexpected event in which participants come to rest on the ground, floor, or other lower level” [21].Health care resource use: Resource use data will be collected during follow-up to measure health service utilization related to falls. This includes ambulance attendances, accident and emergency visits, general practitioner consultations, and hospital admissions (public or private). This will be analyzed descriptively as a secondary outcome and will inform the cost-effectiveness analysis.

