### Statistical Analysis

All statistical analyses will be performed using Stata (StataCorp) or SPSS (version 28, IBM Corp; 2021).

Baseline demographic and clinical characteristics will be summarized by trial arm using means and SD, or median and interquartile ranges for continuous variables, as appropriate, and frequencies with percentages for categorical variables.

The primary analysis will be conducted following the intention-to-treat (ITT) principle, including all participants providing evaluable outcome data irrespective of their engagement with the KOKU program or control intervention.

BBS will be analyzed using a mixed model for repeated measures (MMRM). The model will include the fixed effects of trial arm (ie, KOKU and control), time point (ie, 6 and 12 wk), and the fixed covariate of baseline scores, as well as the interactions of all fixed terms by time point, ensuring the effects are permitted to vary for each of the 2 time points. An unstructured covariance matrix will be used, and the model will be fitted using restricted maximum likelihood (RML) estimation. The primary comparison of interest is between group differences at 12 weeks. Results will be presented as regression coefficients with 95% CIs. Continuous secondary outcomes will be analyzed using a similar framework to the primary outcome.

The rate of falls will be analyzed using a parametric model for count data (eg, Poisson or negative binomial), adjusting for baseline values. The appropriate model will be chosen depending on the distribution of this variable. The incident rate ratio will be presented with a 95% CI.

All the models will be adjusted for baseline values. Thus, to minimize data loss, simple mean imputation (across the randomized groups) of the corresponding outcome data will be used. MMRM models are likelihood-based and therefore consistent with the missing-at-random assumption. Sensitivity analyses to assess the robustness of the MAR assumption will be performed for the primary outcome.

Quantitative data will be managed using REDCap [26], a secure, web-based software platform designed to support data capture for research studies, providing (1) an intuitive interface for validated data capture; (2) audit trails for tracking data manipulation and export procedures; (3) automated export procedures for seamless data downloads to common statistical packages; and (4) procedures for data integration and interoperability with external sources.

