### Strengths and Limitations

This study has several strengths. Firstly, it employs an RCT design, minimizing bias and allowing for robust comparisons between the intervention and control groups. Secondly, by using the BBS as the primary outcome measure, the study employs a well-validated and clinically relevant tool to assess balance changes. Balance is widely used as a proxy for falls risk due to its being a key risk factor for falls. As a modifiable risk factor, physical interventions that target balance can directly reduce falls risk. Many falls prevention guidelines recommend balance training with improvements in balance considered a marker of intervention success [7]. Thirdly, the trial incorporates an economic evaluation, which is important for informing policymakers and health care providers about the cost-effectiveness of digital interventions, particularly those tested in real-world conditions. Additionally, by utilizing an intention-to-treat analysis, the study findings will reflect real-life effectiveness in practice.

Despite its strengths, the study has several limitations. In exercise studies, it is very difficult to blind participants or assessors, which can lead to bias. Furthermore, although unlikely, it is possible that participants in the intervention group could share information so that those in the control group have access to the intervention given that some participants were recruited from the same care providers. In addition, larger, fully powered studies are also needed to investigate the clinical and cost-effectiveness of the KOKU intervention with a primary outcome of fall rates.

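### A suspected adverse reaction ends study participation, not only the exercise; this undercuts the intention-to-treat aim and the 6-month falls record, with losses likely mainly in the KOKU arm

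*Protocol article*

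**What the plan says.** All references are to the protocol article.

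- **Adverse Events and Risk.** The main concern is stated as "whether or not the participant can come to any harm from using the KOKU digital program". The rule is "Any participant suspected of having an adverse reaction will be immediately withdrawn from the study". The cause is then to be investigated, and the following sentence leaves seriousness and causality to the Principal Investigator. The section gives no expected rate: "No disproportionate adverse events are expected".
- **Statistical Analysis.** The primary analysis is intention-to-treat (ITT), "including all participants providing evaluable outcome data irrespective of their engagement with the KOKU program or control intervention". On missing data, "MMRM models are likelihood-based and therefore consistent with the missing-at-random assumption", and "Sensitivity analyses to assess the robustness of the MAR assumption will be performed for the primary outcome".
- **Outcomes.** "Falls and all injuries will be recorded during the 6-month period", by daily calendars over 24 weeks. The Berg Balance Scale (BBS) and EQ-5D-5L are collected at weeks 6 and 12.
- **Strengths and Limitations.** ITT is claimed as a strength: "by utilizing an intention-to-treat analysis, the study findings will reflect real-life effectiveness in practice".
- **Randomization and Blinding.** Neither the researchers who collect data nor the participants are blinded.
- **Intervention.** Controls are also asked to exercise, from a leaflet, 3 times a week.

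**The concern.** The rule removes people from the study, not just from the exercise program, and nothing in the article says that assessments or fall calendars continue afterwards. An ITT analysis depends on following people whatever happens to their treatment. Here an event after randomization, suspected to be caused by treatment, ends follow-up. Because suspicion is enough, someone whose event later proves unrelated has already left.

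The loss is unlikely to be neutral. A fall or injury during exercise is an outcome in its own right and also a plausible trigger for removal, so follow-up can stop because an outcome occurred. People who tolerate the exercises badly may also have worse later balance than their earlier data predict. If such losses are more common with KOKU, the balance comparison tilts toward KOKU. The later safety, falls, quality-of-life and resource-use record of those same people is also cut short.

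**Working it through.** **1. What a withdrawal removes, by timing**

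| Withdrawn | Lost |
|---|---|
| Before week 6 | All post-baseline BBS, so the person leaves the primary analysis; EQ-5D-5L at weeks 6 and 12; remaining fall calendar and resource use |
| Between weeks 6 and 12 | Week-12 BBS and EQ-5D-5L; remaining fall calendar and resource use (a week-6 BBS can still enter the model) |
| After week 12 | Remaining fall calendar to week 24 and the resource use linked to it |

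**2. The plan's sample size, reproduced** (inputs from Sample Size: SD 14, correlation 0.7, difference 5, 90% power, 5% significance taken as two-sided, 13% attrition)

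- Adjusted SD = 14 × √(1 − 0.7²) = 9.998
- n per arm = 2 × [9.998 × (1.960 + 1.282) / 5]² = 84.03, rounded up to 85
- 85 / (1 − 0.13) = 97.7, so 98 per arm and 196 in total. This matches the article.

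**3. Effect on power.** Take an extra KOKU-arm loss on top of 13% in both arms (assumed, since no rate is given). Power = Φ(5/SE − 1.960), with SE = 9.998 × √(1/n₁ + 1/n₂).

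| Extra KOKU loss | 98 / 98 randomized | 102 / 100 randomized |
|---|---|---|
| 0% | 90.4% | 91.2% |
| 2% | 90.1% | 90.9% |
| 5% | 89.6% | 90.4% |
| 10% | 88.6% | 89.5% |

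The loss is at most about 2 percentage points. Power is not the issue.

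**4. Effect on bias.** The planned mixed model adjusts for baseline and uses week-6 data, so the raw gap between retained and withdrawn people is not the bias. What matters is the shortfall *g* of the withdrawn people's unobserved week-12 BBS below the model's MAR prediction. With a share *p* withdrawn:

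Bias in the treatment difference = p(KOKU) × g(KOKU) − p(control) × g(control)

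Setting the control term to zero, in BBS points (and as % of the 5-point target):

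| p (KOKU) | g = 3 | g = 5 | g = 10 |
|---|---|---|---|
| 2% | 0.06 (1.2%) | 0.10 (2%) | 0.20 (4%) |
| 5% | 0.15 (3%) | 0.25 (5%) | 0.50 (10%) |
| 10% | 0.30 (6%) | 0.50 (10%) | 1.00 (20%) |

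For scale, the planning SE of the difference is 9.998 × √(2/85) = 1.53 points, so the range runs from 0.06/1.53 = 0.04 to 1.0/1.53 = 0.65 of an SE. If both arms lost 5% with a 5-point shortfall, the bias would be 0.25 − 0.25 = 0. The size therefore depends on the imbalance between arms.

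**The case against.** Several stronger readings are tempting, and the article does not support them.

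- **That only the KOKU arm loses data.** The rule applies to any participant, and controls exercise too, so they can also have suspected reactions. That losses fall mainly in the KOKU arm is an inference from the section's focus on KOKU and the lack of blinding.
- **That the sections are logically incompatible.** The ITT set is limited to people with evaluable outcome data, so the analysis can be run as written after such withdrawals. The conflict is with the purpose of ITT, and with the falls and injury record promised for 6 months.
- **That harms are hidden.** The triggering event is recorded and investigated, its causality is judged, and related serious events go to the ethics committee. Only what happens afterwards is lost.
- **That every outcome is biased toward KOKU.** For falls, the triggering event would already be counted, and the effect of truncation depends on how exposure time is handled, which the article does not state. For costs the direction is equally open.

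It is also fair that the event rate may be low, that MAR sensitivity analyses are already planned for BBS, that multiple imputation is planned for the economic data, and that a fuller adverse event procedure exists but is not shown. These points limit the size of the problem. They do not remove it: the stated rule creates the missing data, multiple imputation ordinarily rests on MAR as well, and no MAR sensitivity analysis is stated for falls, EQ-5D-5L or costs.

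**Conclusion.** The concern holds in a limited form. As written, the rule ends study participation on suspicion of an adverse reaction. That conflicts with the ITT aim and with the 6-month falls and injury record, whichever arm is affected. The loss is plausibly related to outcome and probably heavier with KOKU, so MAR is doubtful for these participants.

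The size is uncertain. If 2-10% of the KOKU arm is withdrawn, with a 3-10 point shortfall below the model's prediction and no comparable control loss, the BBS effect is overstated by about 0.06-1.0 points. The low end is negligible; the high end is a fifth of the target difference. Both ranges are assumptions, as the article gives no rate. Confidence is high on the wording and the conflict, and lower on arm imbalance and size.

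**What to change.** Reconcile Adverse Events and Risk with Outcomes and Statistical Analysis:

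1. Separate any stop of the exercise (a clinical decision on which no view is taken here) from withdrawal from follow-up. State that BBS, questionnaires and fall calendars continue as scheduled unless the participant withdraws consent, wherever follow-up is still open.
2. For participants already withdrawn under this rule, keep all data held and report their number, timing and reason by arm.
3. Include them in the planned MAR sensitivity analysis for the primary outcome, with a delta-adjusted or control-based scenario for week-12 BBS.

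Recruitment closed in March 2025, so 24-week follow-up would have ended around September 2025, and the article lists only data compilation and analysis as remaining. Items 2 and 3 are therefore probably what can still be done. The cost is some extra reporting and one more scenario in an analysis already promised, plus contact with a few participants if any follow-up is still open.

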### Statistical Analysis

All statistical analyses will be performed using Stata (StataCorp) or SPSS (version 28, IBM Corp; 2021).

Baseline demographic and clinical characteristics will be summarized by trial arm using means and SD, or median and interquartile ranges for continuous variables, as appropriate, and frequencies with percentages for categorical variables.

The primary analysis will be conducted following the intention-to-treat (ITT) principle, including all participants providing evaluable outcome data irrespective of their engagement with the KOKU program or control intervention.

BBS will be analyzed using a mixed model for repeated measures (MMRM). The model will include the fixed effects of trial arm (ie, KOKU and control), time point (ie, 6 and 12 wk), and the fixed covariate of baseline scores, as well as the interactions of all fixed terms by time point, ensuring the effects are permitted to vary for each of the 2 time points. An unstructured covariance matrix will be used, and the model will be fitted using restricted maximum likelihood (RML) estimation. The primary comparison of interest is between group differences at 12 weeks. Results will be presented as regression coefficients with 95% CIs. Continuous secondary outcomes will be analyzed using a similar framework to the primary outcome.

The rate of falls will be analyzed using a parametric model for count data (eg, Poisson or negative binomial), adjusting for baseline values. The appropriate model will be chosen depending on the distribution of this variable. The incident rate ratio will be presented with a 95% CI.

All the models will be adjusted for baseline values. Thus, to minimize data loss, simple mean imputation (across the randomized groups) of the corresponding outcome data will be used. MMRM models are likelihood-based and therefore consistent with the missing-at-random assumption. Sensitivity analyses to assess the robustness of the MAR assumption will be performed for the primary outcome.

Quantitative data will be managed using REDCap [26], a secure, web-based software platform designed to support data capture for research studies, providing (1) an intuitive interface for validated data capture; (2) audit trails for tracking data manipulation and export procedures; (3) automated export procedures for seamless data downloads to common statistical packages; and (4) procedures for data integration and interoperability with external sources.

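### As written, the mean-imputation rule covers the 24-week fall counts and would dilute the fall-rate ratio; the baseline value in the falls model is also undefined

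*Protocol article*

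**What the plan says.** All references are to the protocol article.

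- **Outcome (Outcomes).** "Falls will be assessed using daily self-report fall calendars for 24 weeks". Falls are therefore counted prospectively after baseline.
- **Model (Statistical Analysis).** "The rate of falls will be analyzed using a parametric model for count data (eg, Poisson or negative binomial), adjusting for baseline values". The choice between the two families is left until the data are seen: "The appropriate model will be chosen depending on the distribution of this variable". The effect measure is to be a rate ratio with its 95% interval.
- **Baseline adjustment (Statistical Analysis).** "All the models will be adjusted for baseline values".
- **Imputation (next sentence, drawn as a consequence of the previous one).** "simple mean imputation (across the randomized groups) of the corresponding outcome data will be used".
- **Pre-trial falls information (Outcomes).** The falls risk tool has an item on "history of any fall in the previous year". The bespoke baseline questionnaire lists fractures, medication, comorbidities, vision and demographics, but not falls.
- **Timing of that tool.** The Outcomes text says that outcome data are taken at baseline, 6 and 12 weeks. In Table 1 the health-questionnaire row, which includes the falls risk tool, has two ticks (read as weeks 6 and 12), whereas the Berg Balance Scale row has three.
- **Incomplete follow-up.** Sample Size allows 13% attrition for the 12-week primary outcome. Adverse Events and Risk says that a participant with a suspected reaction "will be immediately withdrawn from the study". No attrition figure is given for the 24-week calendars.

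**The concern.** Two statements fit the falls model badly.

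First, the imputation sentence follows a sentence about every model and names outcome data. For the continuous outcomes, the text goes on to describe a likelihood-based analysis under missing at random, which needs no imputed outcomes. For falls no other missing-data rule is stated, so an analyst following the text would replace an incomplete calendar with a pooled mean count. That throws away the falls the participant did report and puts the same number into both arms, which shrinks any real difference. The imputed value is also not a whole number, although the model is for counts.

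Second, the model is to adjust for a baseline value, but no baseline fall count is described. The natural candidate is the fall-history item. If it were first asked at week 6 or 12, the previous year would include 6/52 = 12% or 12/52 = 23% of time after randomization, and the answer could not serve as a baseline covariate.

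At stake are the size and power of a secondary comparison, and whether its adjustment is valid.

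**Working it through.** **The plan's own figure.** None is stated for falls. The stated sample size is for the Berg score and is reproduced: residual SD = 14 × √(1 − 0.7²) = 9.998; n per arm = 2 × (1.960 + 1.282)² × 9.998² / 5² = 84.03, rounded up to 85; 85 / 0.87 = 97.7, rounded up to 98; total 196. The 13% attrition therefore belongs to the 12-week outcome.

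**Assumptions for falls (not in the documents).** 0.6 falls per person per 24 weeks in the control arm, true ratio 0.70 (0.42 falls in the KOKU arm), dispersion 1.5, dropout times uniform over follow-up, 98 per arm. Dropout in KOKU against control: 13/13%, 20/6% and 26/0%, each averaging 13%.

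**Expected ratio after pooled-mean imputation.** With dropout d_K and d_C, the pooled completer mean is m = [(1 − d_K) × 0.42 + (1 − d_C) × 0.60] / [(1 − d_K) + (1 − d_C)]. Each arm's mean becomes (1 − d) × its own mean + d × m.

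- 13/13%: m = (0.3654 + 0.5220) / 1.74 = 0.510. KOKU 0.3654 + 0.0663 = 0.4317; control 0.5220 + 0.0663 = 0.5883; ratio **0.73**.
- 20/6%: m = (0.336 + 0.564) / 1.74 = 0.517. KOKU 0.336 + 0.1034 = 0.4394; control 0.564 + 0.0310 = 0.5950; ratio **0.74**.
- 26/0%: m = (0.3108 + 0.600) / 1.74 = 0.523. KOKU 0.3108 + 0.1361 = 0.4469; control 0.600; ratio **0.74**.

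The fall rate cancels from these ratios, so they depend only on the true ratio and the dropout split. If the true ratio is 1, then m equals both arm means and the ratio stays at 1.

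**Simulation (600 runs per scenario, negative binomial, dispersion treated as known).**

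| Dropout | True ratio | Offset: ratio, rejection | Pooled-mean imputation: ratio, rejection |
|---|---|---|---|
| 13/13% | 1.00 | 1.005, 6.0% | 1.000, 4.5% |
| 20/6% | 1.00 | 1.011, 4.8% | 1.005, 3.0% |
| 26/0% | 1.00 | 0.994, 4.3% | 0.993, 3.5% |
| 13/13% | 0.70 | 0.687, 26.5% | 0.725, 19.8% |
| 20/6% | 0.70 | 0.707, 23.0% | 0.750, 16.5% |
| 26/0% | 0.70 | 0.692, 25.0% | 0.744, 17.5% |

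The simulation agrees with the arithmetic to within simulation error (for power, about √(0.25 × 0.75 / 600) = 1.8 percentage points). The loss of power is 6.5 to 7.5 percentage points.

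**Falls discarded.** With 13% dropout in both arms, no treatment effect and dropouts observed for half of the 24 weeks: 196 × 0.13 × 0.5 × 0.6 = 7.6 falls, out of 196 × 0.6 × (0.87 + 0.065) = 110 observed, or about 7%.

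**The case against.** The best defence is that the imputation sentence was meant for missing baseline values only. It is presented as a consequence of the baseline adjustment, and missing outcomes in the repeated-measures model are left to the likelihood. That is probably the intention, but the words name outcome data. For falls the intended reading also leaves a gap, because no baseline falls value is defined.

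A second defence is that the fall-history item is a usable baseline value. The Outcomes text says that outcome data are collected at baseline. The Economic Analysis section adjusts for baseline utility, which comes from a questionnaire in the same Table 1 row, so baseline administration was very likely intended. This stands as far as it goes: the covariate probably exists, but the plan neither names it nor agrees with its own table on timing.

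A reader might go further and infer that, because no exposure term is named, unequal follow-up would produce a spurious fall-rate ratio. The documents do not support that. They promise a rate and a rate ratio, both of which imply person-time, and an article commonly leaves the offset to the analysis plan. The bias would need an offset that is truly omitted and follow-up that differs by arm. If dropouts contribute half of the 24 weeks, 13/13% gives a ratio of 1.00 without an offset; 20/6% gives 21.60 / 23.28 = 0.93. That split is an assumption. The withdrawal rule is not limited to one arm and does not say that a fall is a reaction.

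A reader might also infer inflated type I error from the Poisson option. That would follow only if Poisson were kept despite overdispersion, and the plan names negative binomial and ties the choice to the distribution.

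**Conclusion.** The point holds in a limited form. The imputation rule as worded covers fall counts. Following it would discard observed falls, move a true ratio of 0.70 to about 0.73 to 0.75, and cost 6.5 to 7.5 percentage points of a power that is already only 23% to 26.5% under the assumed inputs. The error is towards no effect; nothing here creates a false one. These figures rest on the assumed dropout splits, and the power figures also on the assumed fall rate and dispersion. The documents supply none of these for falls.

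Separately, the baseline value for the falls model is undefined, and the Outcomes text and Table 1 must be reconciled on when the falls risk tool is given.

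The weight is modest: falls are a secondary outcome, and the article itself says that larger studies are needed with fall rate as the primary outcome. Recruitment has closed, but the article places the analysis after its own publication, so the wording can still be settled.

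**What to change.** 1. Confine simple mean imputation to missing baseline covariates, and state that fall counts are not imputed.
2. Analyse the falls actually observed by negative binomial regression, with arm as a factor and log(calendar days observed) as offset. The offset makes explicit the person-time that the rate ratio already implies and keeps the falls reported before dropout. Report the rate ratio with its 95% CI as planned.
3. Reconcile the Outcomes text with Table 1. If the falls risk tool was completed before randomization, name any fall in the previous year (yes/no) as the baseline covariate. If it was not, do not use a later answer in its place.

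The cost is wording only, with no new data. Fixing negative binomial in advance loses negligible precision if the counts prove to be Poisson.
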